### Acupoints used in the treatment group

The stimulation points in the intervention group will be RN12 (Zhongwan), RN6 (Qihai), ST36 (Zusanli, bilaterally), SP6 (Sanyinjiao, bilaterally), SP9 (Yinlingquan, bilaterally), SP10 (Shuidao), RN3 (Zhongji), and RN2 (Qugu). All acupoints are located according to the National Standard of People's Republic of China (GB/T 12346-2006). The acupoint diagram is shown in Additional file 2.

### Sham acupoints used in the control group

To ensure the quantity of stimulus is uniform between two groups, the same kind, size, and the number of needles will be used for the control group. However, the control group will be treated with shallow needling at the non-meridian and non-acupoint positions. The acupuncture points shifted 1-inch from the actual location and have no therapeutic value.

### Permitted and prohibited concomitant treatments

Both groups can receive conventional treatment for prostate cancer (such as endocrine therapy) and/or pelvic floor muscle training, which differ from acupuncture principles. Researchers need to keep a detailed record. Treatments like the principles of acupuncture are not allowed.

### Outcome measures

#### Primary outcome measures

##### International Consultation Incontinence Questionnaire-Urinary Incontinence Short Form (ICIQ-UI-SF)

Scores of the scale will be calculated to investigate the incidence of urinary incontinence and the impact of urinary incontinence on patients. It will be evaluated at baseline, and at 6, 12, 18, and 24 weeks post treatment. The scale is shown in Additional file 3.

#### Secondary outcome measures

##### One-hour pad test

It is a test to objectively evaluate urinary incontinence. It is measured to assess the change in volume of urine leakage from baseline at weeks 4 and 6.

##### Seven-two-hour voiding diary

On the basis of not changing life status and urination habits, 72 h of fluid intake and urination time are continuously recorded every week. It is used to assess the change in mean 72-h incontinence-episode frequency (IEF) from baseline and at weeks 1, 2, 4, 6, 12, 18, and 24. The scale is shown in Additional file 4.

##### EPIC-26

The Expanded Prostate Cancer Index Composite 26-item version includes three categories of questions aimed to evaluate the prostate function and QoL of patients with prostate cancer in the past 4 weeks. Evaluated at 6, 12, 18, and 24 weeks, changes in scores from the baseline will be analyzed. The scale is shown in Additional file 5.

##### SAS

Self-Rating Anxiety Scale is a 20-item self-report assessment used to measure anxiety levels, based on the scoring of 4 groups of symptoms: cognitive, autonomic, motor, and central nervous system symptoms. The scores will be evaluated at 6, 12, 18, and 24 weeks, and changes in scores from the baseline values will be analyzed. The scale is shown in Additional file 6.

##### Weekly consumption of pads

Changing and average weekly consumption of pads at 1, 2, 4, 6, 12, 18, and 24 weeks from the baseline will be calculated.

##### Severity of urinary incontinence

It will be evaluated at 6, 12, 18, and 24 weeks. The change in the number and percentage of severity ratings from the baseline value will be analyzed.

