**Methods:**

Twenty hospitals will recruit 340 participants with urinary incontinence after radical prostatectomy in China from April 2021 to April 2022. Participants will be randomly allocated to acupuncture or sham acupuncture with a 1:1 ratio using computerized simple random sampling. The study plan consists of 1-week baseline, 6-week treatment, and 18-week follow-up. Eighteen 30-min sessions of acupuncture or sham acupuncture treatment will be provided between weeks 1 and 6. The primary outcome is the change in the International Consultation on Incontinence Questionnaire-Urinary Incontinence Short Form (ICIQ-UI-SF) score at the week 6 from the baseline. Secondary outcomes include the change in volume of urine leakage at weeks 4 and 6 from a baseline measured using the 1-h pad test; 72-h incontinence episode frequency based on a 72-h voiding diary; change in the Expanded prostate cancer Index Composite scale (EPIC-26); change in the Self-Rating Anxiety Scale; weekly consumption of pads; and the severity of urinary incontinence based on a 72-h bladder diary and self-assessment of the therapeutic effect. The safety of acupuncture will also be assessed.

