### Statistical methods

#### Sample size calculation

By enrolling approximately 340 (170 in each group) participants, the study will provide 90% power to detect a between-group difference of 2.5 in reduction of ICI-Q-SF score from baseline using a 2-sided alpha level of 0.05, and assuming a common standard deviation of 6.3 and a dropout rate of 20%. A difference of 2.5 points in the ICI-Q-SF score was selected for sample size calculations, which is indicative of a clinically significant change [24–26].

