#### Statistical analysis

Summary tables (descriptive statistics and/or frequency tables) will be provided for all variables as appropriate. The primary outcome analysis will use the Cochran-Mantel-Haenszel (CMH) test. For continuous variables, means and standard deviations will be presented, unless the variable has a skewed distribution, in which medians, 25th and 75th percentiles will be presented. For other categorical data, between-group comparisons will be performed using a Wilcoxon rank-sum test, chi-square test, or Fisher’s exact test, as appropriate. AE incidences for each treatment group will be tested by the *χ*^2^ test or Fisher’s exact test as appropriate. All the statistical analysis will be performed using SAS version 9.4 (SAS Institute Inc) with 2-sided tests at a significance level of < 0.05. We will use the multiple imputation to handle missing data.

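### The severity outcome is worded as a change in group counts and percentages; an ordered comparison of each man's category, adjusted for his baseline category, would use data already collected at almost no cost

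*Protocol article*

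**What the plan says.** Under Severity of urinary incontinence (Secondary outcome measures), the protocol article gives the timing, "It will be evaluated at 6, 12, 18, and 24 weeks", and the quantity, "The change in the number and percentage of severity ratings from the baseline value will be analyzed". The abstract bases the rating on a 72-hour diary. Table 1 marks it at baseline (W0) and at W6, W12, W18 and W24.

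The neighbouring outcome SAS (Self-Rating Anxiety Scale) is worded differently: "changes in scores from the baseline values will be analyzed". A score belongs to one patient, so that phrase describes a change within a man.

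Under Statistical analysis, the rule for categorical outcomes other than the primary is: "For other categorical data, between-group comparisons will be performed using a Wilcoxon rank-sum test, chi-square test, or Fisher’s exact test, as appropriate". None of the three tests is assigned to severity. The same section adds, without limiting it to any outcome: "We will use the multiple imputation to handle missing data".

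Under Sample size calculation, the plan works with 170 men per arm, "assuming a common standard deviation of 6.3 and a dropout rate of 20" per cent.

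**The concern.** The sentence fixes what is analysed, and it names a tally. Three things follow if it is carried into the analysis as it stands.

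- A change in the number of men in a category mixes change in severity with loss to follow-up.
- Baseline and follow-up tallies come from the same men, but the tally drops the link, so improvement and worsening cancel out of sight.
- The listed tests, applied to the ratings at one visit, leave out the baseline rating. Chi-square and Fisher's exact test would leave out the order of the categories as well.

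At stake are the clarity and efficiency of one secondary outcome. The primary outcome is the ICIQ-UI-SF score.

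**Working it through.** **1. The plan's own figure.** No figure is given for severity, so the sample size serves as the starting point. Inputs from Sample size calculation: difference 2.5, SD 6.3, two-sided alpha 0.05, power 90%, dropout 20%.

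n per arm = 2 × (1.960 + 1.282)² × 6.3² / 2.5² = 133.5, rounded up to 134. Dropout: 134 / 0.80 = 167.5, rounded up to 168 per arm, 336 in total, against 340 stated. The figure reproduces. It concerns ICIQ-UI-SF only. With 170 per arm, 170 × 0.80 = 136 men per arm are expected at follow-up.

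**2. Count and percentage when nobody changes category.** Assumption: 60 of 170 men per arm are severe at baseline (60/170 = 35.3%), and dropout is unrelated to severity.

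| Dropout | Severe men left | Change in count | Severe share of men left |
|---|---|---|---|
| 20% | 60 × 0.80 = 48 | -12 | 48/136 = 35.3% |
| 25% | 60 × 0.75 = 45 | -15 | 45/127.5 = 35.3% |
| 15% | 60 × 0.85 = 51 | -9 | 51/144.5 = 35.3% |

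The count falls, and differs by 6 men between arms that lose 25% and 15%. The percentage does not move.

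When dropout does depend on severity, the percentage moves too. Assumption: mild/moderate/severe 34/68/68 at baseline, 136 of 170 men kept, nobody changing.

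| Retention (mild/moderate/severe) | Severe men left | Change in count | Severe share |
|---|---|---|---|
| 80/80/80% | 54.4 | -13.6 | 40% to 40% |
| 100/90/60% | 40.8 | -27.2 | 40% to 30% |
| 40/80/100% | 68 | 0 | 40% to 50% |

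**3. What the tally hides.** With full follow-up, let the margins go from 34/68/68 to 68/68/34. Two sets of individual moves give exactly these margins:

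- 34 men move from moderate to mild, 34 from severe to moderate, and 102 stay: 68 improve, 0 worsen.
- 34 move from moderate to mild, 34 from severe to mild, 34 from severe to moderate, 34 from mild to moderate, 34 from moderate to severe: 102 improve, 68 worsen.

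The change in number and percentage is the same in both.

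**4. What the baseline rating is worth.** Simulation under assumed inputs: a latent normal severity cut into four ordered categories, 136 men per arm, a shift of 0.35 SD between arms at follow-up, and latent correlation of 0.5 to 0.7 between baseline and follow-up. Ranges cover these correlations and different runs and cut-points.

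| Test | Power |
|---|---|
| Chi-square on the follow-up rating | about 53-61% |
| Wilcoxon rank-sum on the follow-up rating | about 70-77% |
| Rank test stratified by baseline category | about 78-93% |

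With no effect, all three reject in about 5% of trials, so the gaps are gaps in efficiency, not in validity.

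**The case against.** The strongest reply is that this is one loosely worded sentence in a condensed article, and that number and percentage is the usual way to summarise a categorical variable. Much of that stands, and it rules out several stronger readings that a reader might infer.

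- *That there is nothing at patient level to test.* Table 1 records severity for each man at baseline and four later visits, and those ratings can be compared between arms. What is not defined is a change, or a baseline-adjusted comparison, at patient level.
- *That the analysis ignores order.* Wilcoxon is on the list and uses order. The plan neither assigns it to severity nor rules out the other two tests.
- *That dropout alone will produce an apparent benefit.* The percentage, which is the other half of the same definition, stays at 35.3% in both arms in the first example above. It moves only if dropout is related to severity, and such dropout can also bias a complete-case analysis of individual ratings.
- *That missing ratings are left unhandled.* Multiple imputation is planned without restriction. Applied to each man's rating, it keeps the denominator constant and removes the count artefact.
- *That leaving out baseline is an error.* In a 1:1 randomised trial, comparing follow-up ratings between arms is valid without it.

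The reply does not remove the difference in wording from the SAS outcome, or the fact that none of the listed tests uses the baseline category. Imputation restores the denominator but does not bring the pairing into the comparison.

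**Conclusion.** The point holds as a minor one. The severity outcome is worded as a group tally: its count depends on retention if taken literally, and its margins do not show who moved. The listed tests are valid on the ratings at a visit but leave the collected baseline category unused; chi-square or Fisher would also discard order.

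The size rests on assumptions. The documents give no number of categories, no severity distribution and no expected effect on severity, so the 60/170 and 34/68/68 splits, the dropout patterns and the simulation inputs are illustrations. Only the ordering of the three power figures is informative, not their level. That the tally belongs to each arm is an inference, though the natural one in a two-arm comparison. The primary outcome, the 340 men and the 90% power are not affected.

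**What to change.** Replace the second sentence of Severity of urinary incontinence with wording such as: *Each participant's severity category at weeks 6, 12, 18 and 24 will be compared between arms as an ordered outcome, adjusted for his baseline category. Missing ratings will be imputed for each participant. Counts, percentages and a table of shifts from baseline to each visit are descriptive.*

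Name one method in advance under Statistical analysis, for example a rank test stratified by baseline category or a proportional-odds model with baseline category as covariate.

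The cost is wording in two sections. No data are added, because the rating is already scheduled at baseline and at all four later visits, and the sample size does not change.

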##### Self-report assessment of therapeutic effect

A 4-point scale is used: no help, little help, medium help, and great help [24]. Treatment effects will be evaluated at 6, 12, 18, and 24 weeks.

### Safety assessment

To exclude any related serious diseases, patients will be asked to undergo necessary inspection before randomization, including vital signs, blood routine, urine routine, biochemical items, ECG. These tests will be performed at the week 6 of the study to evaluate the safety of this trial. If any AEs occur during the trial, patients will be treated as soon as possible.

### Adverse events

With any adverse events during treatment, protective therapeutic measures shall be taken in time to ensure the safety of participants. According to the different levels of adverse events, researchers will make the judgment if the participants will continue, suspend, or withdrawal from the study. Common treatment-related AEs including fainting during acupuncture, local bleeding, sticking of needle, subcutaneous hematoma, and itching at the sites of needle insertion. If the patient has an adverse event due to acupuncture and the investigator decided that the patient would not suitable to continue to participate the trial, the patient will be weeded out consequently.

### Data management

All information related to this study, including but not limited to the following documents: research protocol, informed consent, CRF, investigator manual, training materials, research protocol, subject grouping information, statistical report, and research conclusion, must be strictly confidential. All personnel involved in the study shall sign a confidentiality undertaking. The CRF is composed of paper form and electronic form. The monitor (CRA) shall check out the CRF on site to ensure the consistency between the paper CRF and the electronic CRF regularly. The revealed problems shall be corrected and the name of the corresponding researcher should be signed after verification with the researcher. In order to ensure the accuracy of data, the researcher shall carefully fill in the CRF paper and upload the data into the electronic CRF. The revealed problems during the uploading process should be registered and reported to CRA. After all signed documents match the requirements of the research protocol, the database will be locked by the data management unit, and no data can be modified after locking the database.

### Quality control

The design and implementation of multicenter clinical research require the cooperation of departments, and we established committees as listed below: ① The Expert Committee: the expert committee participated by clinical experts, statistical experts, and quality control experts. They are responsible for building the principles of clinical research methodology and ensure its scientificity, rationality, and feasibility of the protocol; they solve the major problems in the enforcement process of clinical research. ② The Executive Committee: the members have practical experience in clinical research, familiar with clinical research operation procedures and specifications, and they also possess the ability of medical information retrieval, communication, coordination, and organization. They are responsible for formulating of a research plan and informed consent and complete the project initiation application procedure. ③ The Data and Safety Monitoring Committee (DSMC): which is composed of independent third-party experts and does not belong to any institution of this study, to independently evaluate safety indicators and put forward audit suggestions based on the analysis results of safety indicators, thereby protecting the rights and security of participants. During the implementation of this study, members of the committee will regularly receive the research progress report issued by the Executive Committee every 3 months and hold open meetings to listen to the research process report from the research project leader. ④ The Data Management and Statistical analysis Center: its responsibilities include the establishment of data randomization systems and electronic database, case report form (CRF) design, data analysis, and verification.

### Statistical methods

#### Sample size calculation

By enrolling approximately 340 (170 in each group) participants, the study will provide 90% power to detect a between-group difference of 2.5 in reduction of ICI-Q-SF score from baseline using a 2-sided alpha level of 0.05, and assuming a common standard deviation of 6.3 and a dropout rate of 20%. A difference of 2.5 points in the ICI-Q-SF score was selected for sample size calculations, which is indicative of a clinically significant change [24–26].

#### Statistical analysis

Summary tables (descriptive statistics and/or frequency tables) will be provided for all variables as appropriate. The primary outcome analysis will use the Cochran-Mantel-Haenszel (CMH) test. For continuous variables, means and standard deviations will be presented, unless the variable has a skewed distribution, in which medians, 25th and 75th percentiles will be presented. For other categorical data, between-group comparisons will be performed using a Wilcoxon rank-sum test, chi-square test, or Fisher’s exact test, as appropriate. AE incidences for each treatment group will be tested by the *χ*^2^ test or Fisher’s exact test as appropriate. All the statistical analysis will be performed using SAS version 9.4 (SAS Institute Inc) with 2-sided tests at a significance level of < 0.05. We will use the multiple imputation to handle missing data.

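### The primary analysis is a Cochran-Mantel-Haenszel test of unstated form, although the primary outcome is a numeric score change and the trial is sized on a 2.5-point difference in means

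*Protocol article*

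**What the plan says.** The abstract (Methods) defines the endpoint: "The primary outcome is the change in the International Consultation on Incontinence Questionnaire-Urinary Incontinence Short Form (ICIQ-UI-SF) score at the week 6 from the baseline". Table 1 schedules this score at baseline and week 6.

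The section Sample size calculation treats it as a difference in means: "the study will provide 90% power to detect a between-group difference of 2.5 in reduction of ICI-Q-SF score from baseline". The test is two-sided at the 5% level, and the calculation is made "assuming a common standard deviation of 6.3 and a dropout rate of 20" per cent. It describes 2.5 points as a clinically significant change.

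The section Statistical analysis then names one primary test: "The primary outcome analysis will use the Cochran-Mantel-Haenszel (CMH) test". It gives no strata, scores, categories or responder cut-off. For continuous variables it specifies only descriptive summaries (mean and SD, or median and quartiles). The general rule for comparing groups reads: "For other categorical data, between-group comparisons will be performed using a Wilcoxon rank-sum test, chi-square test, or Fisher’s exact test, as appropriate". Multiple imputation is planned for missing data.

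**The concern.** The endpoint and the sample size describe a comparison of two means. The Cochran-Mantel-Haenszel (CMH) test is best known as a test for stratified contingency tables, and the word *other* in the next comparison rule suggests that the primary outcome has been classed as categorical. Read together, these sections state no analysis that estimates the 2.5-point difference on which the trial is sized and clinical relevance is judged.

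Two things are at stake. The first is the scale of the result: a p-value alone cannot show whether the effect reaches 2.5 points. The second is power: the named test covers forms that differ widely in power, and the text does not say which is meant.

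**Working it through.** **Inputs from the protocol article.** Difference 2.5, SD 6.3, two-sided alpha 0.05, power 90%, dropout 20%, 170 per group (Sample size calculation); 20 hospitals with 17 patients each (Randomization and blinding).

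**Step 1: reproduce the stated sample size.** For two means, n per arm = 2 × (1.960 + 1.282)² × 6.3² / 2.5² = 133.5, so 134. The exact t-test gives 134.4. Dividing 134.4 by 0.8 gives 168 per arm, or 336 in total, against the stated 340. The figure therefore matches a comparison of means.

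Completers per arm: 170 × 0.8 = 136. Standard error = 6.3 × √(2/136) = 0.764. Power = Φ(2.5/0.764 − 1.960) = 90.5% (t-test 90.3%). The 95% confidence interval half-width would be 1.960 × 0.764 = 1.50 points.

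**Step 2: CMH in row-mean-score form on the numeric change.** This was simulated with 4,000 runs, 20 centres of 17, 20% dropout, a true difference of 2.5 and SD 6.3. Power was 90.3% stratified by centre and 90.8% unstratified, against 90.8% for the t-test. Essentially no power is lost.

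**Step 3: CMH on a responder outcome.** The protocol gives no cut-off and no expected sham improvement, so both are assumed. With cut-off c and mean sham improvement m, on normal changes with SD 6.3:

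- sham response p0 = 1 − Φ((c − m)/6.3)
- acupuncture response p1 = 1 − Φ((c − m − 2.5)/6.3)
- power = Φ((|p1 − p0| − 1.960 × se0)/se1), where se0 is the pooled and se1 the unpooled standard error at 136 per arm

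| Cut-off c | Sham mean m | p0 | p1 | Power | Completers per arm for 90% |
|---|---|---|---|---|---|
| 2.5 | 0 | 0.346 | 0.500 | 73.3% | 214 |
| 2.5 | 1 | 0.406 | 0.563 | 73.9% | 211 |
| 2.5 | 4 | 0.594 | 0.737 | 70.8% | 227 |
| 5 | 0 | 0.214 | 0.346 | 68.1% | 241 |
| 5 | 4 | 0.437 | 0.594 | 73.9% | 211 |

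A centre-stratified responder CMH, simulated with cut-off 2.5 and sham mean 2.5, gave 73%.

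**Step 4: a linear model with baseline score as covariate.** The baseline to week-6 correlation r is not in the document; it is assumed to be 0.3 to 0.7, with equal variances at the two times. If 6.3 is the SD of change, the residual SD is 6.3 × √((1 + r)/2).

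| r | Residual SD | Power at 136 per arm |
|---|---|---|
| 0.3 | 5.08 | 98.2% |
| 0.5 | 5.46 | 96.6% |
| 0.7 | 5.81 | 94.4% |

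The protocol does not say whether 6.3 is the SD of the change or of the raw score. If it is the raw-score SD, the residual SD is 6.3 × √(1 − r²), and power is 92.9% (r = 0.3) to 99.6% (r = 0.7). On that reading an unadjusted comparison of change has SD 6.3 × √(2(1 − r)) and power of 79.0% (r = 0.3) to 98.8% (r = 0.7).

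**The case against.** The strongest reply is that generalised CMH includes a mean-score statistic that can be applied to a numeric score, and Step 2 shows that it keeps the planned power. No section mentions a responder or a cut-off. The wording about categorical data is loose in any case, since it lists a rank-sum test there. Strata, covariates and the effect measure are often left to the analysis plan. An unadjusted comparison of change is unbiased under randomisation, so covariate adjustment is a gain in efficiency rather than a correction of error.

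Much of this stands. The test is not invalid, and the loss of power is conditional. What remains is that the article is not silent: it fixes a primary test, words the next rule as if that outcome were categorical, and states no comparison for continuous variables. A later plan could repair this only by reinterpreting or replacing a published sentence.

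A reader might infer three stronger points that the documents do not support:

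- **That baseline is ignored.** It enters the change score by subtraction; it is only not used as a covariate.
- **That CMH cannot be combined with the planned multiple imputation.** With two arms, the mean-score form rests on a stratum-weighted difference and its variance, which can be pooled, and chi-square statistics can be combined by established methods.
- **That the trial will have only about 70% power.** That follows only from a dichotomisation that the protocol never states.

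**Conclusion.** The point holds as a mismatch between the stated primary test and the protocol's own endpoint and sample size. On the mean-score reading the cost is a primary result without an estimate or interval on the 2.5-point scale, with power unharmed. On a responder reading the cost is a fall from 90% to about 68% to 74%, subject to the assumed cut-offs, sham means and normality. The text does not decide between the two readings. The sample size is correct for a comparison of means and need not change. The gain from covariate adjustment is an added benefit that depends on the assumed correlation and on what the SD of 6.3 refers to.

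**What to change.** Replace the CMH sentence with wording such as: *The primary analysis is a linear model (ANCOVA) of the change in ICIQ-UI-SF score from baseline to week 6 on treatment group and baseline ICIQ-UI-SF score; the adjusted mean difference and its 95% confidence interval will be pooled over the multiple imputations by Rubin's rules.* Centre may be added as a factor or random effect. Duration of incontinence could also be a covariate if wanted, since Table 1 records time of incontinence; it has no row for time since surgery.

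Keep CMH for the categorical secondary outcomes (severity of incontinence and self-assessed effect), and name its form and strata there. State whether 6.3 is the SD of the change or of the raw score.

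The cost is one paragraph before database lock. Both scores are already scheduled, and 340 participants remain sufficient for this analysis under the assumptions shown.
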